### Intervention and control groups

#### **A) VR-based MBI group (Intervention group)**

Upon enrolment in the study, participants assigned to the VR-based MBI group will be invited to a briefing session at Lingnan University. The session will take place in a quiet room with suitable lighting and air conditioning. Following the participants' written informed consent, they will be introduced to the VR-based MBI user manual, VR technology after completing a pre-test survey.

During the briefing session, participants will download the VR-based MBI app developed by our research team and familiarize themselves with wearing the JAPAN JTSK 6th generation upgraded version of 3D virtual reality glasses. They will engage in a 5-10 minute exercise within the VR environment, giving them the opportunity to explore different natural sceneries provided

in the app. This exercise aims to acclimate participants to the VR technology and allow them to select environments for their mindfulness practice at home. Participants will be provided with the VR glasses to take home and practice mindfulness for approximately 10-15 minutes daily over the next eight weeks. The app will record their practice time for further analysis. Weekly telephone follow-ups will be conducted to address any questions or concerns, and reminder messages will be sent once a week.

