#### **B) Audio-based MBI group (Control group)**

Participants in the audio-based group will also attend a briefing session where they will receive information on mindfulness practice. They will listen to the same 10-15 minute audio-based MBI instruction as provided in the VR-based MBI app. Similar to the VR-based MBI group, they will receive reminder messages and telephone follow-ups. The only difference between the VR-based MBI and audio-based MBI groups will be the absence of VR technology in the audio-based group.

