#### **C) Usual care group (Waitlist control group)**

The third group will be the waitlist control group, who will not attend any briefing session or engage in mindfulness-based interventions during the pilot period. Instead, they will receive usual care and services provided by community service centres. No additional or new intervention will be provided to them during the study period. We will provide the VR-based MBI to the waitlist control group participants after they have completed the control period.

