| Quantitative assessment | T0 face-to-face survey
Site: Lingnan University                                                                                                                                                                                                                                                                 | T1 face-to-face survey
Site: Lingnan University                                                                                                                                                                                                                                                                                                   | T2 Phone survey                                                                                                                                                                                                                                                       |
| Assessment tool                | 
 
• Basic information (pre-test only)
 
• DASS21
 
• EQ-5D-5L
 
• CZBI
 
• EQ-5D-5L-proxy (Quality of life of care recipients)
 
• Five Facet Mindfulness Questionnaire
 
• ONS4
 
• Relationship Closeness Scale
 
 | 
 
• DASS21
 
• EQ-5D-5L
 
• CZBI
 
• EQ-5D-5L-proxy (Quality of life of care recipients)
 
• Five Facet Mindfulness Questionnaire
 
• ONS4
 
• Relationship Closeness Scale
 
• Treatment Acceptance/Adherence (post-test for VR group only)
 
 | 
 
• DASS21
 
• EQ-5D-5L
 
• CZBI
 
• EQ-5D-5L-proxy (Quality of life of care recipients)
 
• Five Facet Mindfulness Questionnaire
 
• ONS4
 
• Relationship Closeness Scale
 
 |

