### **(iii) Contingency/alternative plan if any problem encountered during implementation**

#### Possible adverse effects of using VR

The common adverse effects of using VR include nausea, eye fatigue (41), dizziness, headache, and motion sickness.(30) The fixed background and short practice time will reduce these adverse effects. During the design stage of the VR-based MBI, relevant procedures will be followed to reduce the adverse effects of using VR and to increase participants' static balance. To manage potential motion sickness, we will prioritize user comfort by gradually exposing participants to VR environments. Additionally, we will optimize the VR experience with stable, natural environments, maintain high frame rates, and provide guidance on minimizing discomfort, including hydration and potential use of ginger supplements or anti-nausea medications.

All participants will be asked at the practice reminders and follow-up if they suffer these side effects. If so, the counsellor will provide counselling on usage of the equipment. If the side effects are severe, the counsellor will ask them to cease use. If a participant reports experiencing emotional difficulty, the research team will also refer them to a specialist or other counsellor.

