Participants will be invited to complete a face-to-face survey before and after the intervention to assess efficacy in terms of target outcomes. At 2-months follow-up, all three groups will be contacted for a telephone survey using the same assessment tools.

- **Adoption by target staff, settings, systems and communities**

We will track relevant participants information for calculating the indicators after recruitment. We will also collect caregivers' feedback on the adoption of the intervention through weekly phone calls and the focus group discussions after the intervention. During the recruitment and after the intervention period, we will also gather staff opinions on how this intervention can be integrated into their existing care practices and services and on the potential for wider adoption of the intervention within their organisation or across other institutions.

- **Implementation: consistency, costs and adaptations made during delivery**

We will track whether the intervention is being delivered as intended and any necessary adaptations made during the study. We will collect feedback from weekly call and focus group discussions after the intervention and exercise time records from the app.

- **Maintenance/sustainment of intervention effects in individuals and settings over time**

The long-term maintenance of the intervention's effects will be evaluated through follow-up assessments with participants and feedback from staff and settings that have adopted the VR-based MBI.

(vii) **Results analysis**

Quantitative data analysis plan

Quantitative data will be analysed using STATA 17.0. By intention-to-treat analysis, participants who are lost or refuse the follow-up will be treated as "no change in psychological well-being". Continuous variables will be checked for normal distribution. First, descriptive analyses will be conducted. Then, paired sample t-tests will be conducted to examine the level of outcome change between pre-test and post-test. Between-group t-tests will also be calculated to detect differences between the intervention and the control groups. A linear mixed-effects model (LMM) will be employed, accounting for both fixed effects (e.g., intervention group, time, and their interaction) and random effects (e.g., individual variability among participants). Confounding variables include demographic variables, self-reported physical health, health condition, social support, technology literacy, social service utilisation (38,39).

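### VR side effects are asked about only to manage them: no survey item, outcome, indicator or analysis captures the answers, so no planned, comparable side-effect rate supports the feasibility conclusion

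*Protocol*

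**What the plan says.** Protocol section c(iii), under possible adverse effects of using VR, states: "The common adverse effects of using VR include nausea, eye fatigue (41), dizziness, headache, and motion sickness". On enquiry it says: "All participants will be asked at the practice reminders and follow-up if they suffer these side effects". What follows is management only: counselling on the equipment, and "If the side effects are severe, the counsellor will ask them to cease use". No form, grading or summary of the answers is mentioned.

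The contacts differ by arm (section c(ii)):

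- VR arm: "Weekly telephone follow-ups will be conducted to address any questions or concerns, and reminder messages will be sent once a week".
- Audio arm: "Similar to the VR-based MBI group, they will receive reminder messages and telephone follow-ups".
- Waitlist: participants "who will not attend any briefing session or engage in mindfulness-based interventions during the pilot period", and no reminders or calls are described for them. They are offered VR once their control period is over, but the protocol does not say whether that is T1 or T2.

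Section c(vi) adds one later contact for everyone: "At 2-months follow-up, all three groups will be contacted for a telephone survey using the same assessment tools".

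The Figure 2 tools at T0, T1 and T2 include no named symptom measure. The only tool added at T1 is the Treatment Acceptability/Adherence Scale, in the VR arm only. Neither the outcomes and RE-AIM indicators in c(v) nor the analysis in c(vii) mentions side effects or stopping because of them.

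**The concern.** The aim in section b is feasibility, acceptability and efficacy of VR-delivered mindfulness at home. Section c(ii) says the VR technology is the only difference between the VR and audio arms, so discomfort from the headset is the natural cost to set against any gain from VR. As written, the pilot could call VR feasible and acceptable with no side-effect rate behind the statement. The sample already leans towards tolerance, because a history of motion sickness is an exclusion criterion.

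Headache, dizziness and eye fatigue also occur without VR. Without a T0 measure and the same question in the other arms, symptoms reported by VR users can be neither attributed to the headset nor discounted. The pilot is meant to inform a larger trial, which would need this information.

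**Working it through.** The protocol gives no side-effect figure to reproduce. Its only relevant number is 30 per arm (3 × 30 = 90, as stated in c(i)).

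**Step 1. Set the enquiry beside the contacts.**

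| Contact | VR | Audio | Waitlist | Symptom data planned |
|---|---|---|---|---|
| T0 survey | yes | yes | yes | none named |
| Reminders and calls, 8 weeks | yes | yes | none described | asked under c(iii); no recording stated |
| T1 survey | yes | yes | yes | none named |
| Focus groups, T1 and T2 | yes | no | no | pros and cons, as themes |
| T2 telephone survey | yes | yes | yes | none named; may be the follow-up meant in c(iii) |

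Two terms in c(iii) are open.

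- *Follow-up* may mean the weekly calls, which the VR-arm section calls telephone follow-ups, or the T2 survey.
- *All participants* may mean all 90 or all VR users. If all 90, the waitlist has no practice reminders at which to be asked. If VR users only, there is no comparator.

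On neither reading is there a baseline value, or a question put to all arms over the same window during the 8 weeks.

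**Step 2. Check the other routes.** The focus groups are planned as 3-4 groups of 5-6 at each timepoint, so 3 × 5 = 15 to 4 × 6 = 24 of the 30 VR participants, and they yield themes, not a rate. The acceptability scale has 10 items and is given once, in the VR arm only; the protocol does not say that any item concerns symptoms. The app records practice time, which can show that use stopped but not why.

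**Step 3. What 30 VR users could show if the answers were recorded.** Rates here are assumptions, with no dropout.

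Chance of at least one case, 1 − (1 − p)^30:

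- p = 2%: 45%
- p = 5%: 79%
- p = 10%: 96%

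Exact (Clopper-Pearson) two-sided 95% limits for x of n = 30, with lower limit the 2.5% quantile of Beta(x, n − x + 1) and upper limit the 97.5% quantile of Beta(x + 1, n − x):

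- 0/30: 0 to 1 − 0.025^(1/30) = 11.6%
- 3/30: 2.1% to 26.5%
- 6/30: 7.7% to 38.6%

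**Step 4. Why a comparator matters.** At an assumed background of 10% to 20%, 30 untreated people would be expected to report 3 to 6 cases (30 × 0.10 and 30 × 0.20). A VR count of 6/30 with no comparator could therefore be entirely background.

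**Step 5. Limit of the comparison.** For 30% v 10%, the 95% half-width is 1.96 × √(0.3 × 0.7/30 + 0.1 × 0.9/30) = 1.96 × 0.10 = 19.6 percentage points. Power is 49% at an assumed two-sided 5% level; for 20% v 5% it is 42%.

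**The case against.** A reader might infer that the pilot can yield no tolerability information at all. The documents do not support that. VR participants are to be asked at weekly contacts, which could give a count over a denominator of 30. On the literal reading audio participants are asked too, which would give a randomised comparator differing only in the headset. What is missing is a commitment to record and report the answers, not the possibility of doing so.

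A reader might also infer that the waitlist can never be asked. That goes too far as well, since the T2 call reaches all three arms. But T2 falls two months after the exposure period, its tool list has no symptom item, and the waitlist may already have used VR by then. It does not supply a concurrent untreated rate.

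The subsection concerns VR equipment, so *all participants* may simply mean VR users. In that case the mismatch is loose wording and a waitlist rate was never promised. This stands as a fair reading, but the absence of any outcome is unaffected by it.

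Tabulation of adverse events is often left to an SAP or case report form, and neither is shown. That is why the point concerns what is scheduled for collection: an SAP cannot recover a T0 value, or a waitlist T1 value, that was never measured.

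Finally, the intervals above would be as wide after the change. They describe any proportion in 30 people and do not measure the defect.

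**Conclusion.** The point holds in limited form. The protocol provides for asking about five VR side effects in order to manage them, but plans no recorded, comparable rate in any arm to inform its conclusion on feasibility and acceptability. Informal counts remain possible from weekly contacts. Two terms in c(iii) need reconciling with the arm-specific contacts.

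The loss is a descriptive result: a rate per arm with wide limits, such as 7.7% to 38.6% for 6/30, set against audio and waitlist. A firm between-arm comparison is out of reach at 30 per arm with or without the change. The analysis of psychological well-being is not affected. The conclusion assumes that no unseen case report form already schedules a symptom measure in all arms; the rates used are illustrative.

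**What to change.** 1. Add one brief checklist covering the five symptoms named in c(iii) (present in the past week, with severity) to the existing T0 and T1 surveys in all three arms. Make it identical everywhere, self-completed, and placed after the outcome scales so that the blinded research assistant does not learn the arm.

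2. Add to c(v), as descriptive feasibility outcomes with exact 95% intervals:
   - the share with any new or worse symptom at T1 relative to T0, over the same one-week window in every arm, with VR v audio as the main contrast and the waitlist as background;
   - separately, symptoms logged at the weekly calls, VR v audio only;
   - separately, the number in the VR arm who ceased use because of side effects at any time, so that people who stopped early and recovered before T1 are not missed.

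   The first and second measures must not be pooled. Doing so would set eight weeks of enquiry in two arms against one week in the waitlist and understate the background.

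3. Reconcile *all participants* and *follow-up* in c(iii) with the contacts each arm has in c(ii) and c(vi), and state when the waitlist control period ends.

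The cost is about a minute per survey, a log on calls already planned, and protocol wording. No extra visit or staff is needed.

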### **(iv) Cross-sector collaboration**

A project team will be formed including investigators of Lingnan University (LU), Chinese University of Hong Kong (CUHK), The University of Hong Kong (HKU) collaborating with

service providers from three DECCs, i.e., Yan Oi Tong, The Neighbourhood Advice-Action Council, Caritas District Elderly Centre-Yuen Long, and Pok Oi Hospital [name] Yuen District Elderly Community Centre. The team will meet regularly to design the training, intervention, and operation of the project.

**(v) Indicators and targets**

- **Reach**

Reach indicators encompass the number of dementia caregivers who express interest in participating and those who actually engage in the program, and the representativeness of participants considering their demographic characteristics.

Qualitative feedback on barriers and facilitators affecting recruitment will be gathered from participants and local stakeholders.

- **Effectiveness**

Overall evaluation plan is shown in Figure 2.

Evaluation of the feasibility and acceptance of VR-based MBI

(Quantitative indicator) At the completion of the intervention, the intervention group will be interviewed to evaluate the acceptability and feasibility of VR-based MBI using the Treatment Acceptability/ Adherence Scale with 10 items (31) .

(Qualitative indicator) Participants will be invited to discuss their experiences of MBI via the VR technique, enabling their comments and suggestions to be collected, and the pros and cons of the VR technique discussed.

Evaluation of efficacy of VR-based MBI

(Quantitative indicators) The primary outcomes will be participants' psychological well-being (measured by the Depression, Anxiety, Stress scale (21 items) (32) and the Chinese Version of the Personal Well-being ONS4 (4items) (33). The secondary outcomes will include (a) Cantonese Zarit Burden Scale Short Version (34); (b) caregivers' health-related quality of life measured by the EUROHIS-QOL 5-Item Index (35); (c) caregivers' mindfulness level measured by the five-facet mindfulness questionnaire (36) ; and (d) carer-patient relationship measured by the Relationship Closeness Scale (37).

- **Adoption**

At the setting level, quantitative adoption indicators will encompass the percentage of participants from various recruitment channels, reasons for setting exclusions, participation rates of approached settings, and a comparison of participating settings with non-participants based on characteristics.

At the staff levels, adoption evaluation will involve gathering qualitative feedback on intervention delivery, such as reasons driving adoption or non-adoption of the intervention, and how the intervention could be integrated into their existing practices and services, along with their feedback on the potential for broader adoption within their organisation or beyond.

For caregivers, qualitative methods will be employed to assess their participation and experiences during the intervention period.

- **Implementation**

Implementation will be evaluated by monitoring the percentage of intervention sessions that are delivered as intended, any adaptations made to the intervention during the study, any additional costs incurred, and the consistency of intervention delivery across different study arms.

We will also collect qualitative feedback on the barriers and facilitators encountered during the implementation process and the overall challenges faced by participants and staff.

- **Maintenance**

Maintenance will be assessed by tracking the retention rate of participants who continue to engage with the VR-based mindfulness intervention beyond the initial trial period. We will conduct a 2-month follow-up assessment to evaluate whether the benefits observed during the study are sustained over time. Additionally, we will gather qualitative feedback from multiple stakeholders to assess the intervention's integration into existing practice and the support required to maintain intervention effectiveness.

(vi) **Evaluation plan (RE-AIM framework)**

- **Reach of the target population**

During the recruitment and implementation, we will track the number of dementia caregivers who show interest in the program and those who proceed to participate. We will also collect demographic data from participants to assess how well they represent the target population of dementia caregivers in Hong Kong. Additionally, we will gather qualitative data through weekly call, focus groups and stakeholder interviews to understand the factors that influence recruitment and participation.

- **Effectiveness (or Efficacy)**

Evaluation of the feasibility and acceptance of VR-based MBI

After completing the 8-week intervention, the VR-based MBI group will participate a survey to evaluate the acceptability and feasibility. Meanwhile, a longitudinal **qualitative** element of the study will be included by undertaking face-to-face focus group discussions with participants in the VR-based MBI group at the completion of the intervention and at 2-months follow-up. It is envisaged there will be 3-4 focus groups, each including 5-6 participants, at each timepoint. The PA and Co-As will facilitate the focus group discussions employing a semi-structured interview method will be adopted. The group discussions will be audio-recorded.

Evaluation of efficacy of VR-based MBI

Participants will be invited to complete a face-to-face survey before and after the intervention to assess efficacy in terms of target outcomes. At 2-months follow-up, all three groups will be contacted for a telephone survey using the same assessment tools.

- **Adoption by target staff, settings, systems and communities**

We will track relevant participants information for calculating the indicators after recruitment. We will also collect caregivers' feedback on the adoption of the intervention through weekly phone calls and the focus group discussions after the intervention. During the recruitment and after the intervention period, we will also gather staff opinions on how this intervention can be integrated into their existing care practices and services and on the potential for wider adoption of the intervention within their organisation or across other institutions.

- **Implementation: consistency, costs and adaptations made during delivery**

We will track whether the intervention is being delivered as intended and any necessary adaptations made during the study. We will collect feedback from weekly call and focus group discussions after the intervention and exercise time records from the app.

- **Maintenance/sustainment of intervention effects in individuals and settings over time**

The long-term maintenance of the intervention's effects will be evaluated through follow-up assessments with participants and feedback from staff and settings that have adopted the VR-based MBI.

(vii) **Results analysis**

Quantitative data analysis plan

Quantitative data will be analysed using STATA 17.0. By intention-to-treat analysis, participants who are lost or refuse the follow-up will be treated as "no change in psychological well-being". Continuous variables will be checked for normal distribution. First, descriptive analyses will be conducted. Then, paired sample t-tests will be conducted to examine the level of outcome change between pre-test and post-test. Between-group t-tests will also be calculated to detect differences between the intervention and the control groups. A linear mixed-effects model (LMM) will be employed, accounting for both fixed effects (e.g., intervention group, time, and their interaction) and random effects (e.g., individual variability among participants). Confounding variables include demographic variables, self-reported physical health, health condition, social support, technology literacy, social service utilisation (38,39).

Qualitative interview—intervention evaluation

After each focus group, digitally recorded audio files will be saved and transcribed by the RA into text. Nvivo 11 will be used for qualitative data analysis. Significant non-verbal and para-linguistic conversations related to participants' experiences of using VR-based MBI will also be noted and recorded. Thematic analysis will be utilized for data analysis, following six steps of thematic analysis, ensuring familiarity with the data, generating initial codes, searching for themes,

reviewing themes, defining and naming themes, and producing the report (40). The PA and RA will use open- coding to identify relevant content in the transcripts. Then the PA will classify all labelled content into several independent themes showing distinct features of the participants' feedback. Results will then be discussed and consolidated in panel meetings with other CoAs.

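### Investigators from the team that designed the VR intervention moderate its focus groups and sort and consolidate the themes, which leaves a risk of unknown size that unfavourable views are withheld or under-weighted

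*Protocol*

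**What the plan says.** Four parts of the protocol assign the relevant roles.

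- **Origin of the app** (c(ii), A) VR-based MBI group): at the briefing, "participants will download the VR-based MBI app developed by our research team".
- **Design of the intervention** (c(iv) Cross-sector collaboration): the project team combines investigators from three universities with service providers, and "The team will meet regularly to design the training, intervention, and operation of the project".
- **Moderation** (c(vi) Evaluation plan, feasibility and acceptance): "The PA and Co-As will facilitate the focus group discussions". These are held in the VR arm only, after the intervention and again at two months.
- **Analysis** (c(vii) Results analysis, qualitative interview): open coding is shared between the PA and the RA. The step that follows is given to one person: "Then the PA will classify all labelled content into several independent themes". The last step goes to the wider group of investigators: "Results will then be discussed and consolidated in panel meetings with other CoAs".

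The protocol names no moderator from outside the designing team and no second person who assigns text to themes. The Blinding section covers only the RA who collects post-test data and does not reach the focus groups.

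**The concern.** Acceptability is one of the stated aims of the pilot (section b), and the focus groups are one of the ways it is evaluated. They also feed the reach, adoption and implementation evaluations in c(vi). Two mechanisms could tilt what they yield. Participants may soften criticism when the people asking for it belong to the team that made the product. An investigator committed to the intervention may also, without intending to, sort or merge critical remarks so that they carry less weight. Both act in the same direction, towards a more favourable picture.

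The pilot is meant to inform a larger trial (c(i)), so a problem with VR that is not voiced, or is lost in sorting, may not be corrected in its design. Who moderates and who classifies is fixed by this protocol and is not a detail normally left to a statistical analysis plan.

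**Working it through.** No sample size, power or error rate is involved, so the check traces roles through the text. It takes the PA and Co-As to be among the investigators whom the protocol places on the project team.

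**Step 1: who does what**

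| Task | Assigned to | Section |
|---|---|---|
| Develop the app | the research team | c(ii) A |
| Design the intervention | project team, including investigators | c(iv) |
| Moderate the focus groups | PA and Co-As | c(vi) |
| Transcribe | RA | c(vii) |
| Open coding | PA and RA | c(vii) |
| Classify into themes | PA | c(vii) |
| Consolidate | panel meetings with the other Co-As | c(vii) |

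The RA takes part in transcription and open coding. Moderation, classification and consolidation all rest with the PA or Co-As. A complaint that is voiced will thus be transcribed by the RA and open to coding by a second person. No second person is named for deciding which theme it enters or how prominent it becomes. A complaint that is never voiced cannot be recovered at any later step.

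**Step 2: how much material is involved**

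Inputs from c(vi): 3 to 4 groups of 5 to 6 participants at each of 2 time points. From c(i): 30 participants in the VR arm.

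- Attendees per time point: 3 × 5 = 15 to 4 × 6 = 24.
- Share of the VR arm: 15/30 = 50% to 24/30 = 80%.
- Transcripts over both time points: 3 × 2 = 6 to 4 × 2 = 8.

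The plan is consistent with the arm size, and a second assignment to themes covers at most eight transcripts.

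**Step 3: what else informs acceptability**

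| Source | Section | Reached by the concern? |
|---|---|---|
| Practice time recorded by the app | c(ii) A, c(vi) | No, recorded automatically |
| Continued use after the trial period | c(v) Maintenance | Not through moderation or theme sorting |
| 10-item Treatment Acceptability/Adherence Scale | c(v), Figure 2 | Not through theme sorting; given by interview with no interviewer named, so courtesy cannot be excluded |
| Weekly calls | c(ii) A, c(vi) | Outside the focus groups; the caller is not named |
| Questions about side effects | c(iii) | Outside the focus groups; a counsellor responds |

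The concern therefore bears on the qualitative strand and not on the acceptability evaluation as a whole.

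**The case against.** The strongest reply is that the protocol already has checks. Sessions follow an interview guide and are audio-recorded, and both advantages and drawbacks of VR are to be discussed. The RA transcribes and shares the open coding, and a panel discusses the results. Developers piloting a product also have reason to want complaints, since these help them improve it. Investigator-led groups in a 90-person pilot are a common-sense use of limited staff, and nothing in the text is misstated or contradictory. All of this is fair. It narrows the concern, but it does not supply a second judgement at the theme stage or a moderator from outside the designing team.

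A reader might go further than the documents allow in five ways.

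- **That no step is kept separate from the designers.** The RA's part in transcription and coding contradicts this.
- **That the focus groups are the main source on problems with VR.** No section says so, and several other channels exist.
- **That participants face the app's makers in person.** The app is credited to the research team collectively. The text does not say which investigators built it, so some Co-As may have had no part.
- **That the coupon buys favourable comment.** It is paid for attending a session, whatever is said there.
- **That the tilt can be expressed as a percentage.** Any complaint rate or withholding rate would be invented, and a thematic analysis does not estimate a share of complainants.

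**Conclusion.** The point holds as a weakness in how roles are allocated. Investigators from the team that designed the intervention moderate the VR focus groups, the PA classifies the coded content, and the Co-As consolidate it. This leaves a risk that unfavourable views are withheld or under-weighted in the qualitative part of the acceptability evaluation.

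The direction is a reasoned inference from courtesy towards developers and from commitment to one's own intervention. The size is unknown. The conclusion assumes that the PA and Co-As share in the team's design work, which c(iv) supports for the investigators as a group but not person by person. It does not show that acceptability will be overstated overall, that the focus-group results would be invalid, or that a decision on a larger trial would change. The protocol sets no rule that ties such a decision to the themes. This is a cheap improvement worth making, not a flaw that undermines the pilot.

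**What to change.** **Section c(vii), qualitative analysis.** Have the PA and the RA who already codes assign the coded content to themes independently. Resolve differences in the panel meeting that is already planned. Report unfavourable as well as favourable feedback under each theme. The RA already handles these transcripts, so this gives that person no new information about allocation. The RA also belongs to the research team, so the gain is a second judgement and not an outside one.

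**Section c(vi), focus groups.** Moderation should move if the team already has a member who did not design the app, did not make the weekly calls and is not a blinded outcome assessor. That person would lead the groups with the existing interview guide, without the app's designers in the room. The protocol does not show that such a person exists. If there is none, keep the present arrangement and report the moderators' role in developing the intervention as a limitation.

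**Cost.** One more pass over at most eight transcripts. If moderation moves, there will be less expert probing during the discussions. The choice of moderator should be settled before the first focus group, because views withheld there cannot be recovered in analysis.
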